## Abstract

Exercise therapy in the intermediate stages of peripheral artery disease (PAD) represents an effective solution to improve mobility and quality of life (QoL). Home-based programs, although less effective than supervised programs, have been found to be successful when conducted at high intensity by walking near maximal pain. In this randomized trial, we aim to compare a low-intensity, pain-free structured home-based exercise (SHB) program to an active control group that will be advised to walk according to guidelines. Sixty PAD patients aged > 60 years with claudication will be randomized with a 1:1 ratio to SHB or Control. Patients in the training group will be prescribed an interval walking program at controlled speed to be performed at home; the speed will be increased weekly. At baseline and after 6 months, the following outcomes will be collected: pain-free walking distance and 6-min walking distance (primary outcome), ankle-brachial index, QoL by the VascuQoL-6 questionnaire, foot temperature by thermal camera, 5-time sit-to-stand test, and long-term clinical outcomes including revascularization rate and mortality. The home-based pain-free exercise program may represent a sustainable and cost effective option for patients and health services. The trial has been approved by the CE-AVEC Ethics Committee (898/20). Registration details: Clinicaltrials.gov NCT04751890 [Registered: 12 February 2021].

## 1. Introduction

Peripheral artery disease (PAD) of the lower limbs is an underestimated pathology that is highly prevalent in elderly individuals [1]. At an intermediate stage, the symptom of intermittent claudication, defined as cramping pain caused by insufficient oxygen delivery to the working muscles, reduces walking ability. PAD, which, in a percentage of cases, may evolve to critical limb ischemia requiring revascularization and amputation, is primarily associated with a high risk of cardiovascular events [1]. Early management of PAD may reduce patients’ disability and functional decline as well amputations and cardiovascular events. Exercise therapy is recommended as the initial treatment for its effectiveness on the walking disability, with lower morbidity, mortality and healthcare costs compared to endovascular or surgical revascularization [1]. In particular, supervised exercise therapy (SET) programs performed at hospitals are recommended [1,2], as they can significantly improve exercise capacity in patients both with and without claudication and are more effective than unsupervised programs [1,3,4,5,6]. SET, carried out in a hospital under the supervision of qualified healthcare providers, is based on intermittent bouts of treadmill walking (30-45 min per session) until moderate to maximum claudication, alternating with periods of rest, performed at least three times/week for 12–24 weeks [1,5,6]. SET programs have shown superior effectiveness compared to endovascular revascularization [1,7] and have the advantages of persistent benefits [1,8], a favorable risk/benefit ratio, safety and few absolute contraindications [1,2,6,8,9,10]. Unfortunately, SET programs are underutilized [1], not widely available, differently implemented [3] and not attractive to patients due to issues of reimbursement, transportation, awareness, motivation and eligibility [2,10]. SET also has also shown a poor impact on patients’ lifestyles in terms of low long-term adherence rates and high variability in rehabilitative outcomes [5,6,9,11] with a high nonresponse rate (37.5%) [12] and lower benefits paradoxically observed in patients with more severe disability [5].

The recently proposed structured home-based (SHB) exercise programs, carried out in the personal setting of the patient [1,6,13], represent an alternative option [14,15], reducing the barriers to exercise, such as the availability of facilities and funding for SET programs [14,15], transportation time and costs for patients and families [4]. These programs make use of behavioral change techniques, health coaching, and tools for self-monitoring of home exercise sessions [9,16,17]. Appointed healthcare providers prescribe structured programs that are generally based on walking sessions progressively increasing from 10 to 50 min at a self-selected pace or to maximal ischemic leg pain, 3-5 times per week [9,16,17]. In some research, SHB exercise showed significant benefits [5]; in other studies, it improved overground walking only when carried out at high intensity [18,19]; but a trial based on coaching, telephone calls and use of wearable activity monitors showed no improvement [20]. SHB is even less effective than SET but is still recommended with a Class IIa Level of Evidence in the clinical practice guidelines for PAD [1,5]. A patient-centered SHB model, the “test in-train out” program (TiTo), was proposed by Manfredini et al. [21,22,23,24,25] when SHB programs were not yet available. This model contemplates the execution of pain-free exercise completely at home, along with check-ups at the hospital approximately once a month for therapy and adherence evaluation, functional assessment and personalized prescription of exercise.

This patient-oriented program, which is associated with significant improvements in performance and quality of life at discharge, low costs and favorable long-term clinical outcomes [21,22,23,24,25,26,27,28,29], was successfully adapted to dialysis patients [30,31] and stroke survivors [32]. Despite its effectiveness in previous studies, the TiTo program was never compared in a randomized controlled trial to the “usual-care” treatment of PAD by advising a walking regimen as suggested by the guidelines. We hypothesize that the TiTo-SHB exercise program may be superior to the usual care treatment in patients with claudication.

The present trial aims to verify the superiority of the TiTo-SHB model compared to walking advice on physical functioning, hemodynamics and quality of life in a cohort of claudication patients.

## 2. Methods and Analysis

### 2.1. Trial Design

This study protocol is reported according to the Standard Protocol Items: Recommendations for Interventional Trials (SPIRIT) guidelines [33]. The study is designed as a single-center parallel-group randomized controlled trial.

### 2.2. Study Setting

The study will take place, starting from 2021, at Azienda Ospedaliero-Universitaria di Ferrara at the Operative Units of Vascular and Endovascular Surgery and Rehabilitation Medicine. An indoor temperature-controlled environment at the Unit of Rehabilitation Medicine will be identified for the outcome measurements.

### 2.3. Eligibility Criteria

Inclusion criteria: Male and female aged > 60 years old; PAD at Leriche-Fontaine stage IIa or IIb, previously diagnosed by clinical and instrumental examination at the Department of Vascular Surgery according to the published standard [1]. An Echo-Color-Doppler will be performed to assess abdominal aorta and iliac arteries, common, superficial and deep femoral arteries, popliteal arteries and both tibial axes [1].

Exclusion criteria: PAD at stage I or at stage III or higher; Ankle-brachial index > 0.9 or <1.4; major cognitive disorders (identified by a Mini-Mental State Examination score < 18/30 [34]); severe uncorrected anemia (hemoglobin concentration < 10 g/dL); severe cardiorespiratory, neurological, or musculoskeletal conditions contraindicating or inhibiting exercise (e.g., major amputation, heart failure at a New York Heart Association score of III or greater); very good exercise capacity determined by a 6-min walking distance > 500 m.

### 2.4. Recruitment

During the first meeting with potential participants, a physician will explore their interest in taking part in the study. In the event of a positive response, patients will be referred for a screening visit to verify that they meet the inclusion criteria. If a patient meets all criteria, he/she will receive an information sheet on the trial as well as a consent form, and he/she will be encouraged to ask questions at will. After a minimum of three days, the patient will be contacted and asked whether he/she has decided to participate; in the event of a positive response, a meeting will be scheduled to perform the outcome measurements, and in the event of a negative response, the patient will be thanked for his/her consideration. The total numbers of screened and recruited patients will be tracked.

### 2.5. Randomization and Blinding

A team member responsible for the enrollment will generate the allocation sequence on a personal password-protected computer, with access granted only to the research coordinator and the administrator. Then, in order to prevent selection bias, patients will be randomized between the two groups through a computerized randomization stratification approach by an external administrator not involved in the trial. Participants will be stratified by their degree of PAD severity (ankle-brachial index [ABI] > or <0.5) and the presence of diabetes. The randomization scheme (1:1 ratio) will be structured in permuted blocks of 8 to ensure a similar number of participants between groups. Ultimately, each of the subjects will be assigned to receive one of two treatments: TiTo-SHB (experimental group) or walking advice as an active control (C). The participants cannot be blinded to the two interventions, as the training protocol is detailed in the information form. Once randomized, a participant will not be transferred to the other treatment group for any reason (even at the participant’s request), but the treatment may be suspended upon the patient’s request or the physician’s decision.

Researchers responsible for outcome measurement will be blinded to group allocation; unblinding will not be possible for any reason.

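### A team member who enrols patients generates the allocation sequence, so concealment is not assured even though an external administrator assigns patients

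*Protocol article*

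**What the plan says.** All the relevant statements stand in Section 2.5 of the protocol article (Randomization and Blinding).

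- **Generation:** "A team member responsible for the enrollment will generate the allocation sequence on a personal password-protected computer".
- **Access:** "with access granted only to the research coordinator and the administrator". The enrolling team member is not on this list.
- **Assignment:** "patients will be randomized between the two groups through a computerized randomization stratification approach by an external administrator not involved in the trial". The same sentence gives its purpose as preventing selection bias.
- **Structure:** "The randomization scheme (1:1 ratio) will be structured in permuted blocks of 8", with four strata from two binary factors: "Participants will be stratified by their degree of PAD severity (ankle-brachial index [ABI] > or <0.5) and the presence of diabetes".
- **Blinding:** "The participants cannot be blinded to the two interventions", whereas the researchers who measure outcomes are blinded.

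Three other places bear on the point. Section 2.4 describes recruitment: a physician explores interest, the patient is contacted after at least three days, and a measurement session is then booked. Table 2 puts screening and consent at most 15 days before baseline. Section 2.7 places the T0 measurements before randomization.

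**The concern.** Concealment requires that whoever decides whether and when a patient enters cannot know which arm comes next. Section 2.5 gives the enrolling role the task of making the list, which breaks that separation at its source.

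There is room to act on such knowledge. Recruitment involves a conversation about interest, a waiting period and a booking, and the timing or order of entry can shift at each step. Someone who knows the next arm could encourage, delay or discourage a patient, even without intending to.

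Bias that enters this way affects the comparison of 6-minute walking distance and is hard to repair. Section 2.12 allows covariance adjustment when baseline differences appear, but that covers only measured factors. Motivation to walk, for example, is not among the measurements listed. With 60 patients, a small number of steered entries could matter.

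**Working it through.** The protocol states no figure on this point, so the main check is a reading of Section 2.5. A short calculation on the block size follows.

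**Step 1. Does the external administrator close the gap?** The section does not say whether the administrator uses the sequence already generated or produces another.

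- If the administrator applies the team member's sequence, which is the natural reading of the order of the two sentences, the team member's knowledge of it remains.
- If the administrator produces a separate sequence, the sentence on generation serves no purpose and the section is inconsistent.

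Either way the section needs correcting.

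**Step 2. Does restricted access close the gap?** The restriction governs who may open the file. It does not undo what the person who created the file has seen, and the section describes no step that keeps the generator from seeing it.

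**Step 3. Does assessor blinding close the gap?** No. It limits bias in measuring outcomes, whereas selection bias arises before assignment.

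**Step 4. How predictable is the next assignment?**

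- With no information, 50% of guesses are right under 1:1 allocation.
- Someone who has seen the list and can recall it is right 100% of the time.
- Someone without the list, who knows the block size and every earlier assignment in the stratum and guesses optimally, has an expected number of correct guesses in a block of 2m of m + 2^(2m−1)/C(2m, m) − 1/2.

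| Block size | Expected correct guesses | Share |
|---|---|---|
| 8 (planned) | 4 + 128/70 − 0.5 = 5.33 | 5.33/8 = 66.6% |
| 6 | 3 + 32/20 − 0.5 = 4.10 | 4.10/6 = 68.3% |
| 4 | 2 + 8/6 − 0.5 = 2.83 | 2.83/4 = 70.8% |

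Enumerating all 70 balanced blocks of 8 gives the same 5.33. It also shows that on average 1.6 of the 8 assignments (1.6/8 = 20%) are known with certainty, because one arm is used up. These figures apply to completed blocks with a fully known stratum history.

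The block size is thus a secondary matter. Smaller blocks are more predictable when their size is known, so any gain would have to come from varying or hiding the size.

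**The case against.** The strongest reply is that the protocol already has the two usual safeguards, an independent assigner and restricted access, and states why they are there. The enrolling team member is not among those with access. The article is also a condensed account, and details of how the list is handled may stand in the full protocol. In addition, consent and T0 already precede randomization.

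Much of this stands, and it rules out several stronger readings.

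- **That the enroller holds the list.** A reader might infer this from the mention of a personal computer, but the same sentence limits access to two other roles.
- **That allocation is not concealed.** The documents do not establish this, because an external party makes the assignments.
- **That the coordinator's access is itself an enrolment leak.** No section gives the coordinator a recruiting role. The duties stated are the interim analysis and stopping decisions (Section 2.11) and the final dataset (Section 2.13).
- **That every assignment is predictable.** The 100% figure applies only to someone who has seen the list and retains it.

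What the reply does not answer is the statement on who generates the sequence. That is not a detail left to a fuller document: the article states it outright and gives it to an enrolling role. Later restrictions do not reach it.

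**Conclusion.** The point holds in this form: the role that enrols patients also generates the sequence, so concealment is not assured and the protocol's own aim of preventing selection bias is not secured by its text.

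The conclusion assumes that the generator can see the sequence when it is produced, since nothing in Section 2.5 says otherwise. It also takes the administrator in the access clause to be the external administrator in the next sentence.

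The size of any bias in the walking outcome cannot be derived from the documents. The probability of predicting the next assignment lies between 50% and 100%, depending on what the enroller retains. The 67% for fixed blocks of 8 needs complete knowledge of the stratum's history, and the finding does not depend on it. The point warrants an amendment because the remedy is cheap and the bias, if it occurs, cannot be fully corrected afterwards.

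**What to change.** Amend Section 2.5 so that:

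1. The external administrator, who has no role in enrollment, both generates and holds the sequence.
2. Nobody who recruits or enrols patients has access to it.
3. Each assignment is released only once consent, eligibility and the T0 measurements are recorded. T0 before randomization is already planned, so the addition is to make release depend on the record.

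As an optional minor addition, the block size could be withheld from recruiting staff or varied. Simply replacing 8 with smaller fixed blocks would not help.

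The cost is a short amendment. The role and the computerized procedure already exist, and the sample size does not change. The small downside is that site staff lose direct access to the list.

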### 2.8. Sample Size Calculation

Based on published data we observed the variations in 6MWD in TiTo-SHB program and in other trials including groups at usual care [20,23]. Considering a baseline mean 6MWD of 300 m, with 27 patients for each group, the study will have 90% power to confirm the superiority of TiTo-SHB respect to walking advice, with a superiority margin set at the minimal clinically important difference or 36 m [37]. Allowing for a possible 10% dropout rate during the trial, a sample size of 60 patients (30 per group) will be planned.

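### A single published block size of 8, in an open single-centre trial with known strata, makes up to about one assignment in six deducible with certainty by anyone who tallies past allocations by stratum

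*Protocol article*

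**What the plan says.** Section 2.5 of the protocol article fixes one block size at 1:1 allocation: "The randomization scheme (1:1 ratio) will be structured in permuted blocks of 8 to ensure a similar number of participants between groups". It names both stratification factors: "Participants will be stratified by their degree of PAD severity (ankle-brachial index [ABI] > or <0.5) and the presence of diabetes". That makes 2 × 2 = 4 strata.

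The treatment is open: "The participants cannot be blinded to the two interventions, as the training protocol is detailed in the information form". The same section blinds the researchers who measure outcomes and describes nobody else as blinded. Section 2.1 adds: "The study is designed as a single-center parallel-group randomized controlled trial".

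Section 2.5 also contains safeguards. Access to the list is restricted, an external administrator carries out the randomization, and the declared purpose is to prevent selection bias. Neither a varying nor an undisclosed block size is mentioned.

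**The concern.** In a block of 8 with four places per arm, the remaining assignments are fixed as soon as four patients have gone to one arm. Working that out does not require sight of the list. It requires the block size, which is published, and a record of earlier allocations in the same stratum. The two arms look different in practice: section 2.6.1 describes a paced programme with hospital visits, and section 2.6.2 a recommendation to walk. Treating staff therefore know what was allocated. Restricting access to the list does not close this route.

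The stake is selection before randomization. ABI and the 6-minute walk both appear in the eligibility criteria (section 2.3), so a candidate's ABI stratum and walking capacity can be known early. Section 2.4 leaves at least three days between the information sheet and the call-back. If someone knew the next assignment, a fitter or more motivated patient could be encouraged, delayed or discouraged accordingly. The primary outcome is an effort-dependent walking test. Blinded assessment and intention-to-treat analysis do not undo selection that took place before allocation.

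**Working it through.** **Inputs from the protocol article.** Block size 8, ratio 1:1 and four strata (section 2.5). Planned size (section 2.8): "Allowing for a possible 10% dropout rate during the trial, a sample size of 60 patients (30 per group) will be planned". The planned size reproduces: 27 / (1 − 0.10) = 30 per group, 60 in all. The protocol states no figure for predictability.

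**Assumption.** Stratum sizes are not given, so they are varied below.

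**Step 1, one complete block.** With m = 4 per arm, assignment j is forced if the first j − 1 patients have used up one arm. For j > m,

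P(forced at j) = 2 × C(m, j − 1 − m) / C(2m, j − 1).

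- j = 5: 2 × 1/70 = 2.9%
- j = 6: 2 × 4/56 = 14.3%
- j = 7: 2 × 6/28 = 42.9%
- j = 8: 2 × 4/8 = 100%

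The sum is 1.6 forced assignments per block, and 1.6/8 = 20%. Always guessing the arm that is behind is right 66.6% of the time in complete blocks, against 50% by chance.

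**Step 2, 60 patients in four strata.** The last block of a stratum is often incomplete, which lowers the share.

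- Four strata of 15: each has one full block (1.6) plus seven places (0.029 + 0.143 + 0.429 = 0.6), so 2.2. Then 4 × 2.2 = 8.8, and 8.8/60 = 14.7%.
- Highest over all splits, for example 16, 16, 16 and 12: seven full blocks and four unforced places, 7 × 1.6 = 11.2, and 11.2/60 = 18.7%.
- Lowest over all splits, 5, 5, 5 and 45: 3 × 0.029 + (5 × 1.6 + 0.029) = 8.11, and 8.11/60 = 13.5%.
- Stratum sizes drawn at random, with assumed prevalences of 30–50% for diabetes and 15–50% for one ABI category: 9.4 to 9.7 of 60 on average, or about 16% (1 in 6.2 to 6.4).

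**Step 3, effect of varying the block size.** Simulation of 60 patients over four strata, with four assumed stratum mixes from equal to 5/10/25/60%. The guesser is allowed to know the set of possible sizes.

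| | Fixed 8 | Random 6, 8, 10 |
|---|---|---|
| Certain assignments | 15.8–16.2% | 1.6–2.3% |
| Best-guess accuracy | 64.6–64.7% | 64.4–64.5% |
| SD of arm difference (patients) | 2.45–2.49 | 2.38–2.67 |

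A separate calculation with sizes 4, 6 and 8, at 15 patients per stratum, gives the same picture: about 14.7% falls to 2.4%.

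**Step 4, possible bias (illustration; d is assumed).** Suppose all of about 9.6 certain assignments are exploited, 4.8 per arm, each moving that patient's prognosis by d metres in the favoured direction. The unadjusted arm difference shifts by 2 × (4.8/30) × d = 0.32d. For d = 10, 20 and 36 m that is about 3, 6 and 12 m. The yardstick in section 2.8 is "with a superiority margin set at the minimal clinically important difference or 36 m". Partial exploitation shrinks the shift in proportion.

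**The case against.** The strongest objection is that one in six is a ceiling. Reaching it requires a recruiter who learns every earlier allocation, knows each patient's stratum and keeps four running tallies. The protocol describes none of this. It names two hospital units (section 2.2), a physician who explores interest (section 2.4), a rehabilitation team for the exercise arm (section 2.6.1) and an external administrator. A reader might infer that staff will know one assignment in six, or that the method's protection against selection bias is defeated. The documents do not support either reading. They show only that nothing stated prevents the deduction.

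There are also partial safeguards. Table 2 caps the enrolment window at 15 days before baseline, and delaying a patient helps only if another from the same stratum is randomized meanwhile. Screening and recruitment counts are tracked. Baseline 6-minute walking distance is measured before randomization, and section 2.12 allows analysis of covariance. These limit the harm. However, the adjustment is planned only if baseline differences appear, and it would not reach unmeasured motivation.

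It is fair, too, that varying the block size leaves overall best-guess accuracy unchanged. A person steering on a best guess keeps that edge.

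Finally, section 2.5 has the team member responsible for enrolment generate the sequence, which could expose more than the block size does. That is a separate matter. Correcting it alone would leave a known block of 8 deducible.

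**Conclusion.** The point holds as an inexpensive improvement to the design. With a single published block size of 8, four known strata, one centre and open treatment, a person who influences enrolment and tallies past allocations could be certain of up to about 16% of assignments (13.5–18.7% over all possible stratum sizes). The figure rests on the planned 60 patients and on complete knowledge of earlier allocations within each stratum. The protocol neither says that recruiters have that knowledge nor blinds anyone except the outcome assessors. Nothing here shows that selection has occurred or will occur, and the metres in the illustration depend wholly on an assumed d.

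**What to change.** In section 2.5, replace the fixed block size with: *permuted blocks of randomly varying size (for example 6, 8 and 10) within the same four strata*. Keep the sizes in a document not seen by staff who recruit, treat or assess. If recruitment has begun, apply the change to unopened blocks only, and give recruiting staff no running tallies by stratum.

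The cost is one sentence and a regenerated list in the same computerised system, with no extra patients. The balance between arms stays about the same.
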